07	For female subjects of childbearing potential: use of highly effective contraception with a low failure rate defined as < 1% per year for at least 1 month prior to screening and agreement to use such a method during study participation and for an additional 4 weeks after the end of study drug administration: - Combined (estrogen and progestogen containing) hormonal contraception, - An intra-uterine device (hormone-free), - Progestogen-only hormonal contraception associated with inhibition of ovulation, - An intra-uterine hormone releasing system (IUS) A woman of non-childbearing potential may be included if surgically sterile (i.e., after laparoscopic or hysteroscopic sterilization, hysterectomy or bilateral oophorectomy) or post-menopausal for at least 2 years.	To avoid pregnancies with potential harm to the unborn
08	Right hand dominance (assessed using the Edinburgh Handedness Inventory, and defined as a score ≥ 60)	To minimize variability

**Table 2 Tab2:** Exclusion criteria at screening visit

	Exclusion criteria at screening visit	Justification / rationale
01	Presence of any medical devices (e.g., cardiac pacemaker), implants, or prothesis unless it is beyond discussion that these will not put the subject’s safety during the study at risk and will not interfere with the results of the study.	To avoid interference with the purpose of the study and to ascertain the subject’s good health
02	Known or suspected allergic reactions or hypersensitivity to components of lacosamide (Vimpat®). Second- or third-degree atrioventricular (AV) block.	Contraindications for lacosamide
03	Known or suspected allergic reactions or hypersensitivity to components of pregabalin (Lyrica®).	Contraindications for pregabalin
04	Known or suspected allergic reactions or hypersensitivity to components of tapentadol (Palexia®). Known contraindication for drugs with μ-opioid agonist activity, i.e., significant respiratory depression, acute or severe bronchial asthma or hypercapnia. Present or suspected paralytic ileus. Acute intoxication with alcohol, hypnotics, centrally acting analgesics, or psychotropic drugs.	Contraindications for tapentadol
05	Not willing or able to abstain from changes in physical exercise activities during the study.	To avoid interference with the purpose of the study
06	Any chronic pain condition or recent (i.e., within the preceding 2 years) history thereof.	To avoid interference with the purpose of the study

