19	Evidence or history of alcohol or drug (opioids, amphetamines, benzodiazepines cannabinoids) abuse (as defined by ICD-10 or DSM IV) including positive or missing drugs of abuse screen (urine drugs of abuse test). Consumption of more than 21 alcohol units per week for male subjects and more than 14 units per week for female subjects (1 alcohol unit = 1 beer [12 oz./355 mL] = 1 wine [5 oz./150 mL] = 1 liquor [1.5 oz./40 mL] = 0.75 oz./20 mL alcohol).	To ascertain and protect the subject’s good health and suitability for the study
20	Habitually smoking more than 10 cigarettes, 2 cigars, or 2 pipes of tobacco per day within the last 6 months before enrollment in this trial.	To ascertain the subject’s good health
21	Known or suspected of not being willing or able to comply with the requirements of the trial protocol or the instructions.	To ascertain the subject’s suitability for the study
22	Inability to communicate meaningfully with the trial site staff (e.g., insufficient language skills).	To ascertain the subject’s safety
23	Any person with direct involvement in the trial conduct; any person under the direct supervision of the investigator or dependent on the investigator.	Ethical requirement
24	Blood loss of 500 mL or more (e.g., owing to blood donation) within 3 months before enrollment in this trial.	To ascertain the subject’s suitability for the study
25	Pregnancy, planned pregnancy or lactation.	Ethical requirement to protect the unborn or newborn child
26	Presence of dermatological conditions in the test areas of the study that would prevent the proper application of study procedures, such as electrodes for HFS, pinprick (dermatitis, psoriasis, contact eczema, local changes of the skin due to regularly playing volleyball etc.).	To avoid interference with the purpose of the study
27	Any other reason to exclude the subject according to judgment by the investigator	To avoid interference with the purpose of the study
A set of *temporary exclusion criteria* have also been defined. The subject will not be excluded if some of these temporary exclusion criteria are met during the screening visit. Instead, the first study period may be postponed. Before the start of the first study period, previously met temporary exclusion criteria will be checked again, and their absence will be verified before the screening for the first study period takes place.		

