### Criteria for discontinuing or modifying allocated interventions {11b}

At the start of each of the four study periods, subjects will be excluded from the period if any of the criteria listed in Table 3 apply.

**Table 3 Tab3:** Exclusion criteria at study periods

	Exclusion criteria at study periods:	Justification / rationale
33	For female subjects of child bearing potential: positive or missing pregnancy test	To protect a fetus
34	Positive or missing urine test for drugs of abuse (opioids, amphetamines, benzodiazepines, cannabinoids).	Subject safety and to avoid interactions with, e.g., tapentadol (PD interactions, safety interactions)
35	Blood loss of 500 mL or more (e.g., owing to blood donation) since screening.	To ascertain the subject’s suitability for the study
36	Any other reason to exclude the subject according to judgment by the investigator	To avoid interference with the purpose of the study.
Temporary exclusion criteria at study periods. The subject is not excluded if some of these temporary exclusion criteria are met at screening of the study period. Instead, the study period may be postponed. If this is the case, all temporary exclusion criteria will be checked again.		
37	Alcohol consumption in the last 48 h prior to the study period.	Subject safety and to avoid interactions with, e.g., tapentadol (PD interactions, safety interactions)
38	Intake of any drug including herbal medicines and other remedies except the following: contraceptives; oral paracetamol or ibuprofen up to the maximum recommended dose according SmPC, with last intake for both > 4 days prior to each study period for a self-resolving condition.	As described for screening visit
39	Changes in physical exercise activities, e.g., starting workout/training within 1 week prior to the study.	To avoid interference with the purpose of the study
40	Current pain within the last 4 days before the study period.	To avoid interference with the purpose of the study
41	Any transient, clinically relevant illness within 4 days before the period.	To ensure the subject’s good health
42	Incidentally not willing or able to comply with the requirements of the trial protocol or the instructions or to communicate meaningfully with the trial site staff.	To ascertain the subject’s suitability for the study
43	Incidentally unable to take oral medication.	Requirement for the study

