#### Screening visit

The following will be performed:
Explain the purpose of the research, the extent and burden of the procedures and assessments.Obtain informed consent.Assess subject handedness using the Edinburgh Handedness Inventory.Record demographic data.Record prior and concomitant medication.Record clinically relevant medical and surgical history.Assess inclusion criteria.Perform a focused neurological examination in the presence of any clinically evident sensory disorder and a physical examination if indicated from the medical history.Record a 12-lead electrocardiogram and verify absence of signs of second- or third-degree atrioventricular block.Perform urine pregnancy test.Collect a blood sample to verify normal renal and hepatic functions.Perform urine test for drug abuse (opioids, amphetamines, cannabinoids) and perform alcohol consumption check.Record psychosocial characteristics using patient-reported outcome measures and validated questionnaires.Instruct the subject on the study-specific procedures including how to use the rating scales.Demonstrate the test stimuli that will be used, induce sensitization at the left forearm using HFS, and perform hyperalgesia testing 20 min after induction.Assess exclusion criteria specific for the screening visit.

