**Table 5 Tab5:**
[figure not shown]
Detailed timetable of procedures and assessments in periods 1, 2, 3, and 4

* The PK sample on next day can be taken at any suitable time provided that the exact time of sampling is precisely recorded. ** Hyperalgesia testing at the sensitized and contralateral forearm, harmonized across all four IMI2-PainCare-BioPain RCTs

Procedures, assessments, and events during a period:
The subject will have breakfast at home and arrive at the site at or before 08:00 AM.Record prior and concomitant medication.Urine screening test for drugs of abuse and alcohol consumption check.For female subjects: urine pregnancy test.Reassess subject eligibility for the study according to inclusion and exclusion criteria.Train / instruct again the subject on the study-specific procedures.Complete PROMs assessing subject expectations.Optionally, according to local practices, an indwelling venous catheter will be inserted at the start of each study period and will be left in place for the duration of the study day.HFS will be applied to the left forearm to induce sensitization.IMP administration.A total of 5 blood samples (6 mL each) will be taken as scheduled in Table 5 for pharmacokinetic (PK) analyses. The last sample will be taken on the next day, at any suitable time.One pre-dose and 3 post-dose pharmacodynamic (PD) biomarker assessments will be made as scheduled in Table 5.Hyperalgesia testing at the sensitized and contralateral forearm will be made as scheduled in Table 5, harmonized across all four IMI2-PainCare-BioPain-RCTs.Complete PROMs assessing tiredness and anxiety.Drinks (water or sugared juice, e.g., apple juice) and a light meal will be served as scheduled in Table 5.Instruct the subject not to drive or bike or operate machinery for the entire day (risk of sedation or dizziness caused by IMP). Instruct the participants that they should not drive or bike or operate machinery on the following day if they feel drowsy or dizzy.Upon leaving the trial site, if the subject is feeling drowsy or dizzy, arrange for the participant to be driven home by taxi.

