##### Urine drugs of abuse test

At screening and at the beginning of each period, urine samples provided by the subject will be tested for the presence of opiates, amphetamines, and cannabinoids using suitable validated methods commonly used at the site. This is to avoid that tapentadol (tapentadol has μ-opioid activity) is administered to subjects who have recently taken substances with relevant CNS depressant activity as this may increase the risk of sedation (safety risk if the subject leaves the site, negative impact on study results), dizziness (safety risk), and respiratory depression (safety risk).

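### The urine drug panel described for screening and each period omits benzodiazepines, although exclusion criteria 19 and 34 name them and rely on that test

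*Protocol article*

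**What the plan says.** Two exclusion criteria invoke the urine drug test, and two other places describe what it covers.

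- **Criterion 19** (Eligibility criteria {10}, Table 2, screening) excludes for "Evidence or history of alcohol or drug (opioids, amphetamines, benzodiazepines cannabinoids) abuse", and extends this to a positive or absent result: "including positive or missing drugs of abuse screen (urine drugs of abuse test".
- **Criterion 34** (section {11b}, Table 3, each period) reads "Positive or missing urine test for drugs of abuse (opioids, amphetamines, benzodiazepines, cannabinoids". Its justification is subject safety and interactions with drugs such as tapentadol.
- **Screening visit** (Participant timeline {13}) instructs: "Perform urine test for drug abuse (opioids, amphetamines, cannabinoids) and perform alcohol consumption check".
- **Urine drugs of abuse test** (section {18a}), which applies at screening and at the start of every period, says samples are "tested for the presence of opiates, amphetamines, and cannabinoids using suitable validated methods commonly used at the site". It gives the purpose as avoiding tapentadol being "administered to subjects who have recently taken substances with relevant CNS depressant activity", because of sedation, dizziness and respiratory depression.

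The list of procedures under Table 5 mentions the period urine test without naming any classes, and separately requires staff to "Reassess subject eligibility for the study according to inclusion and exclusion criteria".

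**The concern.** The criteria call for a result that the described test does not produce. Criterion 34 is the sharper case, because its list of classes defines the urine test itself and a missing result is as disqualifying as a positive one. It also stands above the temporary criteria in Table 3, so postponing the period is not its stated remedy.

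What is at stake is safety. The test exists to keep tapentadol away from people who have recently taken CNS depressants. The protocol's own criteria count benzodiazepines among the drugs to be tested for, yet they are the class the panel leaves out. At a site that follows the panel description, undisclosed benzodiazepine use would meet no laboratory check before dosing. With four sites in four countries, sites could also apply different eligibility tests, depending on which list each one follows.

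**Working it through.** No formula applies. The check is a comparison of the lists, reading opiates in section {18a} as opioids.

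| Place | Opioids | Amphetamines | Benzodiazepines | Cannabinoids | Classes |
|---|---|---|---|---|---|
| Criterion 19 (screening) | yes | yes | yes | yes | 4 |
| Criterion 34 (each period) | yes | yes | yes | yes | 4 |
| Screening visit list | yes | yes | no | yes | 3 |
| Urine drugs of abuse test {18a} | yes | yes | no | yes | 3 |
| Procedures under Table 5 | not named | not named | not named | not named | none |

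**Differences**

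- Criterion 19 against the Screening visit list: benzodiazepines only.
- Criterion 19 against section {18a}: benzodiazepines only.
- Criterion 34 against section {18a}: benzodiazepines only.

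No place in the article describes a urine test that includes benzodiazepines.

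**Occasions per subject:** 1 screening + 4 periods = 5 scheduled tests, all affected. Four of the five precede a dose, and one of those four doses is tapentadol. Because treatment is blinded, the check is needed before all four.

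**Consequence at a site that runs the three-class panel**

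1. The benzodiazepine result does not exist for any subject in any period.
2. Criterion 34 excludes on a missing result. Read literally, it removes every subject from every period.
3. If the site instead takes the test as done once the three-class panel is back, the subject is dosed with the benzodiazepine part of the criterion unapplied.

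Neither outcome can be intended. The article gives no rate of undisclosed benzodiazepine use, so the number of doses affected cannot be estimated.

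**The case against.** The mismatch itself is not in dispute. Five points count against giving it much weight.

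1. **The criteria are the operative rule.** Table 3 governs whether a subject enters a period, and reassessment against the criteria is a listed procedure each time. This is a fair point about eligibility. But the article does not say that the criteria widen the panel, and the section that defines the test still names three classes.
2. **Read literally, the error is safe.** A missing benzodiazepine result means exclusion and not dosing. That is true on paper, but it would stop the trial at any site using the described panel. In practice a site is likely to read a completed three-class panel as a test that is not missing.
3. **Criterion 19 is tied less tightly.** Its class list qualifies abuse, and the urine test is added without a list of its own. This stands. The case rests mainly on criterion 34, with criterion 19 in support.
4. **Five occasions is a count of textual mismatches and not of exposures.** This also stands: no drug is given at screening, and tapentadol is given once per subject.
5. **Other safeguards exist.** Criterion 04 covers "Acute intoxication with alcohol, hypnotics, centrally acting analgesics, or psychotropic drugs". Criteria 28 and 38 restrict drug intake, criterion 36 allows investigator judgment, and medication is recorded at each period. These lower the risk, but they depend largely on what the subject discloses, and none is described as a laboratory check for benzodiazepines.

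The reference to methods commonly used at the site does not resolve the conflict, since it concerns the assay and not which classes are tested. Nor does the condensed form of an article explain it, because both lists are printed and they disagree.

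**Conclusion.** The concern holds. The panel description and the criteria that depend on it contradict each other by one class of four, at all five scheduled tests per subject. As written, the described test cannot supply the result that criterion 34 requires.

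This is a minor safety and consistency correction that should be made. It has no bearing on the endpoints, the alpha allocation or the power. The conclusion assumes only that opiates and opioids denote the same class here and that sites may follow the panel as described. It assumes nothing about how often benzodiazepines are taken.

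**What to change.** In both the Screening visit list and the section on the urine drugs of abuse test, name the panel as opioids, amphetamines, benzodiazepines and cannabinoids. It then matches criterion 19 at screening and criterion 34 at each period, and the opiates/opioids wording is aligned as well. Deleting benzodiazepines from the criteria would also remove the contradiction, but it would work against the stated purpose of the test and would need a reason.

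The cost is two wording changes and at most a different test panel on urine already collected. No visit, sample or procedure is added.

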##### Laboratory parameters

At screening, a blood sample will be collected to verify normal renal and hepatic functions, following the recommendations of Breithaupt-Groegler et al. (2017) for trials with clinically established IMPs. Renal function will be assessed using the Glomerular Filtration Rate (GFR, estimated by the MDRD formulae (Modification of Diet in Renal Disease – Annals of Internal Medicine 1999;130: 461–470). Normal GFR is defined as ≥ 60 mL/min/1.73 m^2^. Hepatic function will be assessed by measuring alanine aminotransferase (ALT), aspartate aminotransferase (AST), gamma-glutamyltransferase (GGT), and total bilirubin. Values will be considered as acceptable if they are < 1.1× the upper normal threshold as established by the local laboratory performing the analysis. Laboratory results remain valid if they have been completed within 21 days before the first study period. In other case, a new blood sample collection and analysis will be performed during an optional visit (Fig. 2).

#### Collection of pharmacodynamic data

All participating centers have the equipment and expertise required for acquisition of the pharmacodynamic data. Signal processing of the raw PD data to extract the parameters of interest will be done centrally at UCLouvain using the Letswave 6 Matlab toolbox for the analysis of EEG data (http://letswave.org; UCLouvain).

##### EEG/ERP-derived pharmacodynamic data

The EEG will be recorded continuously during each biomarker assessment time-point, using a multichannel EEG amplifier and digitizer as detailed in a separate operational manual. Setting-up the EEG recording system will require 10–20 min. Actual collection of the pharmacodynamic data will require approximately 30 min. During the entire assessment, subjects will be seated in a comfortable chair. The assessment consists in the serial acquisition of (1) ongoing EEG at rest, (2) PEPs elicited by stimulation of the left forearm, (3) LEPs elicited by stimulation of the left forearm, (4) auditory-evoked potentials (AEPs), (5) LEPs elicited by stimulation of the right forearm, and (6) PEPs elicited by stimulation of the right forearm. This serial acquisition is repeated twice. Each acquisition block lasts approximately 2.5 min. The time course of the assessment is shown in Fig. 4.

**Fig. 4 Fig4:**
[figure not shown]
Time course of each biomarker assessment time-point, during which ongoing EEG, pinprick-evoked potentials elicited by stimulation of the left and right forearm, laser-evoked potentials elicited by stimulation of the left and right forearm, and auditory-evoked potentials will be recorded twice (L: left, R: right)

From the collected EEG data, the following biomarkers will be extracted:
Ongoing EEG. Two 2.5 min recording of ongoing EEG will be performed, while the participant is at rest, and not exposed to any sensory stimuli. Each recording will include 1 min of EEG recording with eyes opened, one 30-s period with eyes closed, followed by a second 1-min recording with eyes opened. A frequency analysis of the magnitude of ongoing EEG oscillations will be used to assess the amplitude of ongoing EEG oscillations within the delta (1–4 Hz), theta (4–7 Hz), alpha (8–12 Hz), beta (15–30 Hz), and gamma (40–90 Hz) oscillations, eyes opened and eyes closed. The signal processing steps are described in the operational manual. This will allow generating the key secondary endpoint “theta_amp” by averaging the amplitude of theta band oscillations across the two 1-min EEG segments eyes opened.Laser-evoked brain potentials (LEP). Brief laser heat stimuli lasting only a few milliseconds will be applied to the skin to activate selectively heat-sensitive nociceptors of the skin, as detailed in the operational manual. The thermal stimuli will be produced by a commercially available infrared neodynium:yttrium aluminum perovskite (Nd:YAP) laser stimulator designed for the recording of LEPs. Intensity of stimulation will be set to consistently activate A-delta and C fiber heat-sensitive nociceptors. The device will be used in accordance with safety guidelines, by trained and authorized personnel, as detailed in the operational manual. The Nd:YAP laser is routinely used for diagnostic purposes [34, 35]. The laser stimulator generates a radiant heat stimulus able to heat the skin above the thermal activation of heat-sensitive nociceptors in only a few milliseconds, without producing any skin lesion. The sensations produced by laser stimuli are often described as a brief pinprick, a light burn, or a diffuse warmth. They may be perceived as unpleasant. On rare occasions, the laser stimulus produces a slight punctuate erythema, which may subsequently become hyperpigmented, but always vanishes completely within a few days [36]. In each of the four LEP recording blocks (two blocks per forearm), the laser stimuli will be repeated 15 times, with a randomly varying inter-stimulus interval. The target of the laser stimulus will be slightly displaced during each inter-stimulus interval, to avoid overheating the skin and/or inducing receptor sensitization and/or habituation. After each laser stimulus, the subject will be requested to rate the intensity of the elicited sensation as detailed in the next section. After each stimulation block, the subject will be requested to rate the unpleasantness of the elicited sensation, as detailed in the next section. This EEG data will allow measuring the average amplitude of the negative-positive (N2-P2) vertex potential elicited by laser stimulation [3], required to generate the primary endpoint “LEP N2-P2_amp,” also used for the key secondary analyses. The processing steps to obtain this measurement are detailed in a separate operational manual.Pinprick-evoked brain potentials (PEP). Preferential activation of mechano-sensitive skin nociceptors will be achieved by applying calibrated mechanical pinprick stimuli using small surface probes. The device, provided by MRC Systems, is detailed in a separate operational manual. The time of contact of the needle with the skin is obtained using an internal switch which generates a trigger marking the onset of each stimulus in the ongoing EEG recording. The stimuli will be applied manually by the operator, as detailed in the operational manual. The sensation generated by pinprick stimulation is most often described as pricking. The probe does not penetrate the skin and, hence, does not produce any lesion. For each of the four PEP recording blocks (left forearm: two blocks, right forearm: two blocks), the pinprick stimuli will be repeated 15 times, with a randomly varying inter-stimulus interval. The target of the pinprick stimulus will be slightly displaced during each inter-stimulus interval, to avoid receptor sensitization and/or habituation. After each pinprick stimulus, the subject will be requested to rate the intensity of the elicited sensation. After each stimulation block, the subject will be requested to rate the unpleasantness of the elicited sensation. This EEG data will allow measuring the average amplitude of the negative-positive (N2-P2) complex elicited by pinprick stimulation [5], required to generate the primary endpoint “PEP N2-P2_amp,” also used for the key secondary analyses. The processing steps to obtain this measurement are detailed in a separate operational manual.Auditory-evoked brain potentials (AEP). In addition to exerting a selective effect on nociception, the medications as well as the procedure used to induce hyperalgesia may induce unspecific changes in brain function, such as changes in the level of vigilance (e.g., drug-induced sedation). For this reason, AEPs will be recorded as a control to assess effects that are not specific for nociception [32]. The AEPs will be elicited by short-lasting auditory stimuli presented binaurally at a comfortable listening level (see separate operational manual). Such as for PEPs and LEPs, the auditory stimuli will be repeated 15 times in each block, with a randomly varying inter-stimulus interval. Such stimuli, delivered using relatively long and variable inter-stimulus intervals, are expected to generate a late-latency negative-positive complex (N1-P2), maximal at the scalp vertex, related to brain functions that are, at least in part, similar to those underlying the LEP and PEP N2-P2 response [37]. For each recording block, the amplitude of the N1-P2 will be measured as detailed in the operational manual.
